## Objectives

The present study aims to examine the associations of two short, behavioral theory–driven professional training programs: one based on SDT and the other grounded in hedonic principles. The primary outcome of interest is health-club attendance over one year. In addition, the study seeks to examine associations with these programs on individual behavioral and motivational outcomes among exercisers. The primary hypothesis is that fitness centers implementing either theory-driven training program will exhibit more favorable individual attendance trajectories over time compared with the control condition. Furthermore, it is hypothesized that the hedonic training approach will be associated with higher attendance than the SDT-based intervention. This expectation is based on (a) the relative ease and immediacy with which the hedonic framework and its context-specific tools and strategies can be applied (Teixeira et al., 2024b) and (b) the theoretical premise that SDT-based behavior change requires a longer period for integration and internalization (Ntoumanis et al., 2021). Secondary hypotheses include the following: (a) both theory-driven interventions will be associated with lower attrition rates than the control group and (b) the interventions will be associated with favorable changes over time in behavioral and motivational constructs, including exercise habit, intention to be physically active, satisfaction of basic psychological needs, behavioral regulation, enjoyment, and positive affective experiences.

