### Statistical methods

Preliminary analyses will be conducted prior to all statistical procedures to examine data quality, missingness patterns, and identify potential violations of statistical assumptions. All analyses are planned to be performed using SPSS v.27.0 (IBM, Co.). The primary outcome of the study is attendance, which will be analyzed both for all fitness center members and separately for those who joined the clubs after the commencement of the study (i.e., after September 1, 2025). Attendance will be operationalized as the individual’s mean weekly attendance within each three-month interval and assessed at four time points during the 12 months of the study (three, six, nine, and twelve months). Primary analyses of attendance will be conducted using linear mixed-effects models (LMMs), with time specified as a within-subject factor and individuals treated as random effects to account for repeated observations. Intervention condition (control, SDT-based training, and hedonic-based training), time, and their interaction will be included as fixed effects, with age and sex included as covariates. These models will be used to characterize and descriptively compare attendance trajectories over time across intervention conditions, with emphasis on the magnitude and direction of longitudinal patterns rather than on individual-level causal inference. Primary analyses will follow an intention-to-treat principle adapted to the cluster-allocated design, such that all eligible individuals are analyzed according to their fitness center’s assigned condition, regardless of attendance patterns or dropout. Linear mixed-effects models were selected because they incorporate all available longitudinal observations under a missing-at-random assumption without requiring imputation.

Because intervention allocation occurs at the fitness-center level and each condition is implemented in a single center, cluster-level variance and intraclass correlation coefficients cannot be estimated independently of condition-related effects. Accordingly, comparisons across intervention conditions are considered exploratory and descriptive in nature. For complementary descriptive purposes, 3 (Condition) × 4 (Time Points) split-plot ANOVAs may be conducted to summarize overall patterns of longitudinal change in attendance. Results from these analyses will be interpreted descriptively, given that intervention conditions are implemented at the fitness-center level.

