Secondary outcomes include dropout and motivational variables. Dropout (membership cancellation) will be examined using administrative records from all members enrolling after September 1, 2025. Dropout rates will be summarized at three-month intervals, and time-to-event analyses will be used to describe adherence patterns over the 12-month period. Percentage attrition rates will be reported descriptively, and Kaplan–Meier survival curves will be used to illustrate the timing of dropout across conditions. Participants who remain actively enrolled at the end of the observation period will be treated as censored observations at their last available follow-up time point. Motivational and behavioral variables will be analyzed in the longitudinal subsample of participants. Changes over time in these variables (baseline, six, and twelve months) will be examined using linear mixed-effects models, with time specified as a within-subject factor and participants treated as random effects. Intervention condition, time, and their interaction will be included as fixed effects, with age and sex entered as covariates. Given the limited number of repeated measurements, models will be specified with a parsimonious random-effects structure. For consistency with prior literature and ease of interpretation, complementary 3 (Condition) × 3 (Time Points) split-plot ANOVAs may also be conducted, with results interpreted descriptively. Effect sizes will be reported as model-based estimates of change over time (e.g., differences in attendance slopes and estimated marginal means), with 95% confidence intervals. Additional control, complementary, and exploratory analyses are anticipated, particularly within ancillary studies.

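### The dropout summaries named for hypothesis (a) carry no age or sex adjustment, although the attendance and motivational models do; standardised figures beside the crude ones would be a minor, cheap improvement

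*Protocol article*

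**What the plan says.** The Objectives section states, as secondary hypothesis (a), that "both theory-driven interventions will be associated with lower attrition rates than the control group". This is a directional comparison between conditions.

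The Statistical methods section sets out the dropout analysis:

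- Population and source: "Dropout (membership cancellation) will be examined using administrative records from all members enrolling after September 1, 2025".
- General method: "time-to-event analyses will be used to describe adherence patterns over the 12-month period".
- Named outputs: attrition percentages, given as description only, and Kaplan–Meier "survival curves will be used to illustrate the timing of dropout across conditions".

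No covariate, stratification, weighting or regression model is attached to any of these.

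The same section treats the other two outcome families differently. For attendance, which is analysed for all members and separately for new members, condition, "time, and their interaction will be included as fixed effects, with age and sex included as covariates". The motivational variables are modelled "with age and sex entered as covariates".

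Three further statements bear on the point. Statistical methods says that each condition is run in one center, and therefore calls comparisons between conditions exploratory and descriptive. Trial setting describes the clubs as alike, including in target clientele. Sample size gives reported one-year attrition of 50–60%.

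**The concern.** Randomising three clubs to three conditions cannot balance who joins each club. If age or sex is related to dropout and the mix of joiners differs, crude percentages and Kaplan–Meier curves by condition differ for that reason alone. Such a difference can look like a training effect or mask one.

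By adjusting for age and sex elsewhere, the protocol treats member mix as worth handling. Dropout is the exception, and no reason is given. Among new members, attendance would be compared with age and sex held constant while dropout would not. If the two results pointed in different directions, a reader could not tell whether the outcome or the adjustment was responsible.

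**Working it through.** **The plan's own figures.** There is no dropout figure to reproduce. The protocol states no expected dropout by condition, no number of events and no target difference. The worked sample size (53 completers, 117 recruited) concerns the motivational subsample and has no bearing here.

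**Inputs from the protocol.** One club per condition; one-year attrition of 50–60%; about 200 new members per club in September, with an unstated number joining later.

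**Inputs that are assumptions.** The share of joiners in a higher-dropout age/sex group, and the dropout risk in each group. The protocol gives neither, so a range is shown.

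**Formula.** With no training effect, crude 12-month dropout in a club is p_low × (1 − s) + p_high × s, where s is the share in the higher-dropout group. The gap between two clubs is therefore (s_B − s_A) × (p_high − p_low). The equivalent hazard ratio is the ratio of 12-month cumulative hazards, ln(1 − B) / ln(1 − A).

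| Case | p_low / p_high | s_A / s_B | Crude A | Crude B | Gap (points) | Equivalent HR |
|---|---|---|---|---|---|---|
| Mild | 50% / 60% | 30% / 40% | 53.0% | 54.0% | 0.10 × 0.10 = 1.0 | ln 0.460 / ln 0.470 = 1.03 |
| Middle | 50% / 65% | 20% / 45% | 53.0% | 56.75% | 0.25 × 0.15 = 3.75 | ln 0.4325 / ln 0.470 = 1.11 |
| Large | 45% / 70% | 20% / 60% | 50.0% | 60.0% | 0.40 × 0.25 = 10.0 | ln 0.40 / ln 0.50 = 1.32 |

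All six crude values lie within the protocol's 50–60%, so overall attrition alone would not reveal the problem. Standardising removes the gap. In the middle case, with clubs of equal size, the pooled share is 32.5%, and both clubs give 0.50 × 0.675 + 0.65 × 0.325 = 54.9%.

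**Mix can also hide an effect.** Assume exponential dropout, a hazard ratio of 2.0 between the two groups and 55% dropout overall at a 50:50 mix. The group risks are then 42.8% and 67.2%. With shares of 40% and 60% and no effect, crude dropout is 52.6% and 57.5%, a gap of 4.9 points. If training in the club with the 60% share truly has a hazard ratio of 0.85, the crude gap is only −0.7 points, against −5.5 standardised. Under a milder assumption (group hazard ratio 1.5, shares 40% and 50%) the mix-only gap is 1.5 points.

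**Scale against sampling error.** At 55% dropout, the standard error of a difference between two clubs is √(2 × 0.55 × 0.45 / n). This is 5.0 points for n = 200, 2.9 for an assumed 600 and 2.2 for an assumed 1,000 per club. A shift of 3–5 points is comparable with sampling error. A shift of 1 point is well below it.

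**The case against.** The strongest reply is that this is a condensed article describing a secondary analysis that is descriptive by design. It commits to time-to-event analyses in general and foresees further control and exploratory analyses; neither phrase excludes adjustment. A mixed model with covariates beside crude survival curves is ordinary practice. The clubs are said to share a target clientele and standardised business practices. With one club per condition, age and sex are only two of many differences that cannot be separated from training.

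Much of this stands. A reader might infer that the plan rules out an adjusted dropout analysis; it does not, it simply names none. A reader might also infer that age and sex are known to be on file for every new member. Table 1 lists sociodemographic data only for the exerciser sample, so their availability is inferred from the attendance model, which cannot be fitted for new members without them. Nor would adjustment put the two outcomes on one population: attendance data require active payment and at least one visit a month, and dropout does not.

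Two parts do not stand. The descriptive label does not explain the difference in treatment, because the attendance comparison is equally descriptive and is adjusted. And this is more than silence on a detail: the article names covariates for every outcome that it models and separately names the dropout outputs, which have none. The statement on clientele is an assertion without age or sex figures. It argues for a small shift, not for none.

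**Conclusion.** The point holds as a minor one. The dropout outputs named for hypothesis (a) are unadjusted, while the other two outcome families are adjusted for age and sex, and allocating one club per condition cannot balance member mix. Under the assumed values above, mix alone moves crude 12-month dropout by roughly 1 to 10 points, at the low end if the clienteles are as similar as stated. That range rests wholly on assumed shares and group risks and shows what is possible; it does not estimate a bias in this trial.

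Two stronger readings go too far. The documents do not show that the dropout result will be biased, because they contain no information on actual mix. Nor would adjustment turn the comparison into a causal one, because all other club differences remain tied to condition.

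**What to change.** Keep the crude percentages and Kaplan–Meier curves. Beside them, report dropout at 3, 6, 9 and 12 months for each condition, standardised for age and sex to the pooled new members of the three clubs. A weighted average of Kaplan–Meier estimates within age-band and sex groups would do. Inverse-probability weighting, or curves from a Cox model with age and sex averaged over the pooled members, would serve equally well. State the age bands or functional form in advance.

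Add three sentences: that age and sex come from the same records that the new-member attendance model requires; that standardisation removes only age and sex mix, with other club differences still inseparable from condition; and that the comparison stays exploratory and descriptive.

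The cost is a paragraph of analysis wording and a little programming. No data are needed beyond those for the attendance model. If age and sex prove unavailable for all new members, that model would need revisiting too.

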### Participant timeline

The study is expected to run between September 2025 and the end of August 2026. The three health clubs will be randomized to the conditions (i.e., control, experimental 1 [SDT-based course], and experimental 2 [hedonic-based course]) at the beginning of this period. Baseline motivation and behavior assessments will be conducted upon enrollment after verification of the inclusion and exclusion criteria. These variables will be assessed again at six and 12 months post-randomization. The training courses will be held at the beginning of September at each club according to the conditions previously randomized. Thereafter, short, individualized discussions with each of the exercise professionals, focusing on reinforcing the ideas presented at the initial training courses and providing support for implementation, will take place approximately 10 to 12 weeks apart until the end of August 2026. The application of the content knowledge delivered during the respective training courses (i.e., frequency and fidelity of implementation) will be assessed during each visit. Attendance and dropout data will be collected continuously. Table 1 presents the participant timeline and sequencing of recruitment, allocation, intervention, and assessments.

**Table 1 tab1:** Participants’ enrollment, allocation, post-allocation, and close-out timeline.

	Study period						
	Enrollment	Allocation	Post-allocation				Close-out
Timepoint	-t1	0	t1	t2	t3	t4	t5
Enrollment							
Eligibility screen	⨯						
Informed consent	⨯						
Allocation (of the clubs)		⨯					
Interventions							
Control			⨯	⨯	⨯	⨯	
Experimental (I)—SDT			⨯	⨯	⨯	⨯	
Experimental (II)—hedonic			⨯	⨯	⨯	⨯	
Assessments							
Club’s members							
New memberships			⨯	⨯	⨯	⨯	⨯
Dropouts			⨯	⨯	⨯	⨯	⨯
Exercise frequency			⨯	⨯	⨯	⨯	⨯
Exerciser’s sample							
Sociodemographic	⨯						
Behavioral regulations	⨯				⨯		⨯
Basic psychological needs	⨯				⨯		⨯
Exercise enjoyment	⨯				⨯		⨯
Attraction-antipathy	⨯				⨯		⨯
Pleasure-displeasure	⨯				⨯		⨯
Preference/Tolerance	⨯				⨯*		⨯*
Exercise habit	⨯				⨯		⨯
Intention to be physically active	⨯				⨯		⨯
State self-control	⨯				⨯		⨯
Professionals							
Course comprehension test			⨯				
Course knowledge application				⨯	⨯	⨯	⨯

t1 = Baseline assessments; t2 = 3 months; t3 = 6 months; t4 = 9 months; t5 = 12 months; * = only agreement items.

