As for the secondary outcomes, these will focus on (i) dropout rates at three-month intervals up until one year, and (ii) motivational variables. In the case of dropout rates, administrative records from all members enrolling after September 1, 2025, will be used. This outcome is derived from the complete population of new members during the intervention period, and the expected number of observed events over the 12-month follow-up is sufficient to support descriptive and time-to-event analyses of attrition patterns across intervention conditions. In the case of the motivational variables, the most restrictive analyses will be conducted in a subsample of exercisers enrolling in September. These participants will be recruited for the longitudinal assessment of behavioral regulation, satisfaction of basic psychological needs, exercise enjoyment, subjective exercise experience, exercise habit, and intention to be physically active, assessed at baseline, six months, and twelve months. Sample size considerations for this subsample were guided by the most restrictive planned within-participant longitudinal comparisons and estimated using G*Power (v.3.1.9.7) (Faul et al., 2009). Using benchmarks from a related work [e.g. (Teixeira et al., 2023; Andrade et al., 2022; Henriques et al., 2023)], a repeated-measures ANOVA assuming a small-to-moderate magnitude of change over time (*f* = 0.20), an *α* level of 0.05, statistical power (1-*β*) of 0.95, three repeated measurements, a correlation between repeated measurements of approximately r = 0.70, and allowing for potential violations of sphericity (*ε* ≈ 0.70), a minimum of approximately 53 participants completing follow-up assessments across the three fitness centers is expected to provide adequate sensitivity to characterize meaningful longitudinal changes in motivational outcomes over time. Linear mixed-effects models will be used for analysis, as they are expected to be at least as efficient as the repeated-measures assumptions used for these calculations and allow the inclusion of all available data in the presence of missing observations. Given that the average attrition rate in Portugal over a one-year period in these contexts has been reported as ranging between 50 and 60% (Pedragosa and Ferreira, 2024), a total sample of approximately 117 participants (≈55% attrition) will be required.

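### With about 55% loss planned, the motivational models leave out the attendance data the trial collects; if leaving follows attendance they can show a false 12-month rise of roughly 0.02 to 0.17 SD

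*Protocol article*

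**What the plan says.** Under Statistical methods, the motivational variables are handled as follows: "Changes over time in these variables (baseline, six, and twelve months) will be examined using linear mixed-effects models". The fixed effects are condition, time and their interaction, with age and sex as covariates and participants as random effects. Attendance is not among the terms.

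Under Sample size, one reason for choosing these models is that they "allow the inclusion of all available data in the presence of missing observations". The attendance paragraph of Statistical methods gives the matching assumption, missing at random with no imputation. Sample size also sets the expected loss. The target is "a minimum of approximately 53 participants completing follow-up assessments across the three fitness centers", and about 117 are to be recruited, using a reported one-year attrition of 50 to 60% in this setting and a working value of about 55%.

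Under Participant timeline, "Attendance and dropout data will be collected continuously". The section on club attendance and attrition rate narrows this: attendance is taken for members who are paying and make at least one visit a month.

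**The concern.** A mixed model fitted by likelihood gives valid estimates under missing at random, but only given what is in the model. Here that is earlier scores, condition, age and sex. A member lost before six months contributes only an enrolment score.

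The protocol's own reasoning makes this assumption doubtful. It sets questionnaire loss from club attrition, so it treats loss as following departure from the club. Its background links pleasure during exercise to later participation. Its hypotheses expect attendance, attrition and motivation to improve together. If motivation falls between waves, attendance falls with it and the member then leaves, earlier scores do not capture the decline. Those who remain look better than the group that enrolled.

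The bias would be upward, which is the direction of secondary hypothesis (b), favourable change over time. It would affect the model-based changes and 95% confidence intervals that the protocol promises. Part of the missing information, attendance before departure, is being collected in any case.

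**Working it through.** **1. The plan's own figure.** Inputs from Sample size: f = 0.20 ("assuming a small-to-moderate magnitude of change over time"), α = 0.05, and power "of 0.95, three repeated measurements, a correlation between repeated measurements of approximately r = 0.70", with ε ≈ 0.70 ("allowing for potential violations of sphericity"). For a within-participant repeated-measures ANOVA:

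- λ = f²·N·m·ε/(1 − r) = 0.04 × 53 × 3 × 0.70/0.30 = 14.84
- df1 = (m − 1)ε = 1.4; df2 = (N − g)(m − 1)ε = 72.8 with one group, 70 with three
- Power = 0.953, so N = 53 is reproduced.
- Inflation for loss: 53/0.45 = 117.8, against about 117 stated; 117 × 0.45 = 52.7. This agrees within rounding and confirms the 55%.

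**2. Yardsticks.**

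- Planning effect as a linear rise: means −d/2, 0, d/2 have SD d/√6, so d = 0.20 × √6 = 0.49 SD.
- Standard error of a change with 53 completers: √(2(1 − 0.70)/53) = 0.106, about 0.11 SD.
- Standard error of a difference in change between two clubs, with 39 × 0.45 ≈ 18 completers each: √(2 × 0.60/18) = 0.26 SD.

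**3. Size of the bias.** Large-sample simulation with no true change, SD 1, r = 0.70 between waves and 55% lost by 12 months. The document does not say what drives loss or how strongly attendance tracks motivation, so both are assumptions. The correlation here runs from 0.2 to 0.5.

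| What drives loss | False rise, planned model (SD) | With attendance as auxiliary (SD) |
|---|---|---|
| Chance, or baseline score | 0.00 | 0.00 |
| Previous quarter's recorded attendance | 0.02 to 0.05 | 0.00 |
| Same-period attendance, assumed on record for everyone | 0.07 to 0.17 | 0.00 |
| Same-period attendance plus current motivation | 0.22 to 0.32 | 0.23 to 0.27 |
| Current unmeasured motivation | 0.35 | 0.34 to 0.35 |

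A second simulation with logistic loss on attendance and correlations of 0.3 to 0.6 gave 0.05 to 0.17 SD without attendance and 0.00 with it.

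Attendance-driven loss therefore gives 0.02 to 0.17 SD. That is 0.02/0.106 ≈ 0.2 to 0.17/0.106 ≈ 1.6 standard errors, or 4% to 35% of the planning effect. In the fourth row attendance does not always help: at correlation 0.2 the false rise went from 0.22 to 0.27, and at 0.5 from 0.32 to 0.23.

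**4. Between clubs.** At correlation 0.3 with same-period attendance, the false rise is 0.092 at 50% loss, 0.103 at 55% and 0.115 at 60%. The contrast of 60% with 50% is 0.115 − 0.092 = 0.023 SD. With lagged attendance it is about 0.01 SD or less. Both are small against 0.26 SD.

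**5. Feasibility at the trial's size.** With 117 members and no attendance recorded after leaving, an attendance-using fit pooled over the three clubs cut a bias of 0.07 to 0.13 SD to about 0.01. Its root mean squared error was equal or lower, and it cost almost nothing when loss was random. Imputing separately within each club of 39 gave a root mean squared error that was no better, or worse.

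**The case against.** **The method is standard and the assumption is open.** A likelihood-based mixed model under missing at random is a respectable choice. Auxiliary variables and sensitivity analyses are often left to an analysis plan, which is not shown. The protocol also plans to examine missingness patterns and allows for further analyses. This limits the point: nothing is contradictory or misstated. But the model terms are fixed in the text, and a concrete improvement exists using data the trial already collects.

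**The bias is conditional.** A reader might infer that a false rise is bound to enter the results. The document does not support that. It does not say what drives questionnaire loss, the 55% is a membership figure applied to questionnaire completion, and under random or score-driven loss the bias is zero.

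**It is not wholly avoidable.** A reader might infer that adding attendance removes the bias. It does so only when loss depends on recorded attendance. If current motivation drives loss, almost all of it remains.

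**Attendance is not held for everyone throughout.** The payment and monthly-visit condition means that a paying member who has stopped coming may have no qualifying record, and nothing exists after cancellation. Linkage of turnstile to questionnaire records is not described. This objection stands, so only attendance before departure can be counted on.

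**The effect on comparisons between conditions is minor.** If the control club loses more members, as hypothesis (a) expects, its false rise would be the larger. A reader might infer that this hides a true effect. At about 0.02 SD against a standard error of 0.26 SD, that is not supported. The protocol also calls these comparisons exploratory and descriptive.

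**Conclusion.** The concern holds in conditional form. The motivational models rest on missing at random given earlier scores, condition, age and sex, with about 55% loss planned. If leaving follows attendance and attendance correlates about 0.2 to 0.6 with motivation, they can show a false 12-month rise of roughly 0.02 to 0.17 SD. At the upper end this exceeds the standard error of about 0.11 SD and is about a third of the 0.49 SD planning effect. At the lower end it is negligible. The correlations and loss mechanisms are assumptions, not figures from the document.

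The issue concerns estimated change over time in secondary outcomes. It does not touch the primary attendance analysis, and it has little bearing on differences between clubs.

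**What to change.** In Statistical methods, prespecify that the motivational scores are also analysed with recorded attendance before departure as an auxiliary variable. Use few summaries, such as mean weekly attendance in months 0 to 6 and 6 to 12 while enrolled. Use either a joint attendance–score model or multiple imputation pooled over the three clubs with condition as a term. Do not impute separately within each club of about 39.

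Report this beside the planned mixed model. Add a not-at-random (delta) sensitivity analysis, because attendance removes only the part of the bias that it explains. Keep the link between turnstile and questionnaire records until this work is done; the Data management section plans an anonymised final dataset.

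The protocol says baseline data stay unanalysed until the intervention ends, so the change can be fixed before results are seen. The cost is a modest amount of extra modelling, with no new data or follow-up. The downside is an auxiliary model that has to be checked and kept small at this sample size.
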